## Abstract

**Background:**

Bipolar disorder patients frequently present recurrent episodes and often experience subsyndromal symptoms, cognitive impairment and difficulties in functioning, with a low quality of life, illness relapses and recurrent hospitalization. Early diagnosis and appropriate intervention may play a role in preventing neuroprogression in this disorder. New technologies represent an opportunity to develop standardized psychological treatments using internet-based tools that overcome some of the limitations of face-to-face treatments, in that they are readily accessible and the timing of therapy can be tailored to user needs and availability. However, although many psychological programs are offered through the web and mobile devices for bipolar disorder, there is a lack of high quality evidence concerning their efficacy and effectiveness due to the great variability in measures and methodology used.

**Methods:**

This clinical trial is a simple-blind randomized trial within a European project to compare an internet-based intervention with treatment as usual. Bipolar disorder patients are to be included and randomly assigned to one of two groups: 1) the experimental group (tele-care support) and 2) the control group. Participants in both groups will be evaluated at baseline (pre-treatment) and post-treatment.

**Discussion:**

This study describes the design of a clinical trial based on psychoeducation intervention that may have a significant impact on both prognosis and treatment in bipolar disorder. Specifically, bringing different services together (service aggregation), it is hoped that the approach proposed will significantly increase the impact of information and communication technologies on access and adherence to treatment, quality of the service, patient safety, patient and professional satisfaction, and quality of life of patients.

**Trial registration:**

NCT02924415. Retrospectively registered 27 September 2016

**Electronic supplementary material:**

The online version of this article (doi:10.1186/s12888-016-1159-0) contains supplementary material, which is available to authorized users.

## Background

Bipolar disorder patients frequently present recurrent episodes and often experience subsyndromal symptoms, cognitive impairment and difficulties in functioning with a low quality of life [1–3], illness relapses and recurrent hospitalization [4]. The number of episodes is an important contributor to the stage progression of the illness from less to more severe presentations and consequently poor outcome. Therefore, early diagnosis and appropriate intervention may play a role in preventing neuroprogression in this disorder [5]. Pharmacological treatments such as mood stabilizers, alone or in combination with antipsychotics, appear to be effective to improve symptoms [6, 7]. However, patients often do not adhere to medication and one third of them discontinue the medication completely, increasing their number of relapses [8]. There is evidence of the efficacy of psychological interventions as an adjunct to pharmacotherapy in bipolar disorder to improve clinical and functional outcomes at follow-up [9], with better adherence [10], prevention and delay of relapse [11, 12] and an improved quality of life for patients [13].

The early stages of bipolar disorder is usually a critical period, and the time during which the disorder causes the most suffering in patients and their families, partly because of the impact the diagnosis and a lack of knowledge about the symptoms. Early educational interventions could increase knowledge and awareness of the illness and treatment adherence and thereby reduce relapses and hospitalizations [14]. Cognitive-behavioral therapy has also proven to be effective in the treatment of bipolar disorder [15, 16]. Other interventions such as interpersonal social rhythm therapy, family-focused therapy and mindfulness approaches are also indicated [9].

However there are several obstacles to the successful implementation of these types of psychological treatments. One of the major problems is the face-to-face nature of therapy that requires the patient and the therapist to be available at the same time. The level of commitment required for such treatments is difficult for many patients. Specifically, the therapy is administered over a long period of time (e.g., 4-6 months) and the sessions take place on a fixed date and at a fixed time (e.g., once a week, lasting 1 h). These aspects of the treatment are associated with a high rate of dropout, especially in more functional patients. Moreover, to implement these intervention programs specialized therapists are needed and there is a gap between availability and demand [17, 18], and hence, in many health systems, the provision of such treatments is limited. Therefore, there is a need to develop effective evidence-based interventions focused on the individual characteristics of patients allowing them to cope better with their symptoms in a way that is feasible and cost effective for healthcare systems [9, 12].

New information and communication technologies represent an opportunity to develop standardized psychological treatments using internet-based tools that overcome some of the limitations of face-to-face treatments, in that they are readily accessible and the timing of therapy can be adjusted to the need and availability of each user. Moreover, such intervention programs offer the possibility of patients self-monitoring and continuously assessing their mood (depressive and manic symptoms) as well as other variables such as sleep or physical and social functioning, with two-way feedback between patients and healthcare providers [19, 20]. This type of intervention facilitates early intervention for subsyndromal symptoms and helps patients become more aware of their illness, manage their symptoms better and improve their lifestyle and attitudes towards medication [21]. Nevertheless, although many online psychological programs for bipolar disorder are offered through the web [21–29] and mobile devices [19, 20, 30–34], there is a lack of high quality evidence about their efficacy and effectiveness due to the variability in measures and methodology used [9].

## Methods

### Objectives

#### General objective

To describe the design of an online psychoeducation treatment using new technologies and to compare its effectiveness with standard treatment in patients with bipolar disorder.

#### Specific objective

To assess the effectiveness of a psychoeducation treatment based on telemedicine versus usual treatment in relation to outcomes in bipolar disorder (patients’ illness awareness, symptoms, functionality, relapses and rehospitalizations)To assess satisfaction with the treatment received and the contact with the health service

### Hypothesis

The online treatment of bipolar disorder will be effective for increasing awareness of the illness, improving depressive and manic symptoms and functionality of patients, and reducing relapses and hospitalizations.Patients receiving online treatment will be more satisfied with the treatment received and their contact with the health service than patients receiving the standard treatment.

## Design

This is a clinical trial is a simple-blind randomized trial within a European project titled “The Future Internet Social and Technological Alignment Research” (FI-STAR), to compare an internet-based intervention with treatment as usual. This clinical trial fulfills with the Standard Protocol Items: Recommendations for Interventional Trials (SPIRIT Checklist) (Additional file 1).

FI-STAR provides a solution for Bipolar Patient Treatment Management (BPTM) in the form of a platform developed to support telecare of bipolar disorder patients. The BPTM platform involves clinical professionals (psychiatrists, psychologists and psychiatric nurses), patients and technicians connected using interfacing systems of the integrated multichannel service center, OSAREAN, which was already in place prior to this project. That is, the proposed solution for these patients has been developed with the internal legacy systems of Osakidetza, the largest important health service provider in the Basque Country.

The platform designed provides advanced communication channels and interaction tools to treat, monitor, support and follow-up patients with bipolar disorder. The treatment consists of online psychoeducation which includes learning sessions (with associated assessment questionnaires) and related psychotherapy exercises. The participants will be able to access the psychoeducation functionalities, whenever and from wherever they choose, using whichever of the possible interfaces (PC, tablet, or smartphone) they have and prefer. The psychiatric personnel defines the patient’s baseline parameters, assigns assessment questionnaires for patient monitoring, specifying how often they should be completed, and sets evaluation rules to generate alerts. Both psychiatric personnel and patients should be able to view follow-up data (progress through the educational material, patients’ notes, changes in monitoring parameters, reported medication intake and any side effects, event log, and patient alerts/notifications).

### Participants

Bipolar disorder patients who meet the inclusion criteria are to be included and randomly assigned to one of two treatment groups. To achieve a power of 80% to detect differences from the null hypothesis, H0: μ1 = μ2, using a bilateral Student’s t test for two independent samples, with a significance level of 5%, 25 patients will be included in the experimental group (tele-care support) and 25 patients in the control group, summing to a total of 50 patients for the study.

### Inclusion criteria

Having a diagnosis of bipolar disorderBeing aged between 18 and 50 yearsBeing in remission (in a euthymic state)Being familiar with current information and communication technologies (computer, tablet and/or smartphone)Being under treatment in the mental health network of the Basque Country (Osakidetza)

### Exclusion criteria

Having hearing or literacy difficultiesHaving a diagnosis of mental retardationNot having access to a smartphone or other suitable deviceHaving manic or depressive symptomatology at the time of inclusion (Hamilton Depression Rating Scale [35, 36] > 16 and Young Mania Rating Scale (YMRS) [37, 38] > 8)Having suicidal ideation

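### The symptom exclusion names mania and depression as alternatives but joins its two cut-offs with *and*, so read literally its numeric rule does not exclude a patient above only one of them

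*Protocol article*

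**What the plan says.** Three places in the protocol article bear on who may enter with symptoms.

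- **Exclusion criteria.** One item excludes patients who have manic or depressive symptoms when they are included. Its lead-in joins the two states with *or*. The brackets that follow give the numeric definition: "Hamilton Depression Rating Scale [35, 36] > 16 and Young Mania Rating Scale (YMRS) [37, 38] > 8". Here the connective is *and*.
- **Inclusion criteria.** Patients must be in remission, which is glossed as euthymia. No scale and no cut-off is attached.
- **Participants.** "Bipolar disorder patients who meet the inclusion criteria are to be included and randomly assigned to one of two treatment groups". The remission requirement therefore applies in addition to the exclusion. The same section sets the size: "25 patients will be included in the experimental group (tele-care support) and 25 patients in the control group".

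Under Assessment, the YMRS is also an outcome measure. Depressive symptoms are measured as outcomes with the BDI-II and the BHS; the Hamilton scale appears only in the exclusion criterion.

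**The concern.** An eligibility rule has to give the same answer whoever applies it. Here the words and the numbers of one criterion give different answers for a patient with symptoms of one polarity only. The brackets are also the only place where the document turns symptom status into scores, so they are what a screener would naturally apply.

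If the literal rule is followed and remission is judged loosely, some patients could enter with raised scores on one scale. Such scores tend to fall over time in any arm. The Statistical analysis section tests baseline against post-treatment within each group by a paired t test, which cannot separate that fall from an effect of treatment. The sample would also be less clearly the euthymic population that the trial describes.

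**Working it through.** The plan states no figure on this point that could be reproduced, and no sample-size, power or error-rate figure depends on it. The check is logical.

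**Step 1: the two readings.** Let D mean Hamilton score > 16 and M mean YMRS > 8.

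- Lead-in (*or*): exclude if D or M.
- Brackets read literally (*and*): exclude only if D and M.

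**Step 2: apply both to example scores.**

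| Hamilton | YMRS | D | M | Excluded under *and* | Excluded under *or* |
|---|---|---|---|---|---|
| 10 | 4 | no | no | no | no |
| 17 | 0 | yes | no | no | yes |
| 25 | 3 | yes | no | no | yes |
| 16 | 9 | no | yes | no | yes |
| 5 | 20 | no | yes | no | yes |
| 17 | 9 | yes | yes | yes | yes |

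The readings agree when neither or both cut-offs are exceeded. They disagree whenever exactly one is exceeded, which is what symptoms of a single polarity look like.

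**Step 3: add the inclusion criterion.** Entry requires remission and no exclusion. A patient at 25/3 or 5/20 passes the literal exclusion rule but should fail a clinical judgement of remission. The gap left by the brackets is therefore closed by judgement, not by a number. Nearer the cut-offs, for example 17/0 or 16/9, that judgement is less certain and screeners may differ.

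**Step 4: where an effect would show.**

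- Weight of one patient: 1/25 = 4% of an arm.
- Within an arm: illustratively, if the patient at YMRS 20 fell only to the cut-off of 8, the fall is 20 − 8 = 12 points, and that patient alone contributes 12/25 = 0.48 points to the arm's mean change. The fall is assumed; the arithmetic shows scale only.
- Between arms: allocation is randomised 1:1 and the ANCOVA uses baseline and post-treatment scores. A fall that happens whatever the arm has the same expectation in both arms, so it adds variance but no bias.

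**Step 5: how many patients.** The document gives no distribution of either score among candidates, so the share above exactly one cut-off cannot be calculated.

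**The case against.** The strongest reply is that the protocol as a whole does not let ill patients in. Eligibility needs every inclusion criterion as well as the absence of exclusions, and remission is required. This stands. A reader might infer from the brackets that the trial admits clearly depressed or clearly manic patients, or that the exclusion contradicts the euthymia criterion. Neither follows: an exclusion that is too narrow sits beside a stricter inclusion criterion without contradicting it. The firm inconsistency lies inside the exclusion sentence itself.

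A second reply is that *and* merely lists the instrument and cut-off for each state just named. That may well be what was meant, and the lead-in supports it. But the reader then has to set aside the literal meaning of the numeric rule, and an eligibility criterion should not depend on that.

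A third reply is that a journal article condenses the full protocol. That would answer an omission. This criterion is stated with its thresholds, and its two halves disagree.

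Two further inferences are tempting and unsupported. One is that the criteria disagree on whether Hamilton scores up to 16 count as remission. The inclusion criterion gives no number, and the exclusion never says that 16 or below is remission, so all that can be said is that euthymia has no stated cut-off. The other is that the treatment comparison is biased. Randomisation and the ANCOVA protect it, and the inability of paired tests to isolate a treatment effect exists under either connective.

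**Conclusion.** The point holds as an internal inconsistency in one exclusion criterion. Taken literally, the only numeric screening rule in the document excludes patients above both cut-offs and leaves those above exactly one to an undefined judgement of euthymia. It therefore does not implement the population that its own lead-in describes, and it allows inconsistent screening.

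Severity is minor to moderate. The plausible consequences are a less well-defined population, some extra variance and larger apparent pre-post change within arms. Each affected patient is 4% of an arm; their number is unknown. The conclusion rests on reading *and* literally and on the absence of any other numeric definition of euthymia in the article. If a fuller protocol states the rule as either threshold, only the published wording needs correcting.

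**What to change.** The sponsor should reconcile the lead-in, the bracketed connective and the remission criterion. The numeric rule should match the lead-in, so that exceeding either threshold excludes, and one definition of euthymia should serve both the inclusion and the exclusion criteria. The choice of cut-offs remains the sponsor's.

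The trial is described as retrospectively registered, so enrolment may already have begun. If so:

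- list, by arm, the enrolled patients who exceeded either threshold at baseline, using the Hamilton and YMRS scores taken at inclusion;
- repeat the ANCOVA without them as a sensitivity analysis, leaving the main analysis on all randomised patients.

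The cost is a change of one word plus a cross-reference between the criteria, possibly a few candidates lost at screening, and one listing and one repeat analysis from scores that screening already requires. The sample size and error rates are unchanged.

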### Randomization

Patients are to be randomly assigned to either a control or an intervention group by permuted block randomization with a block size of 4 and a 1:1 allocation using a computer-generated random sequence. The allocation sequence will be prepared by an independent person not otherwise involved in the trial. The control group will receive the standard treatment (pharmacotherapy and regular sessions with their psychiatrist) and the intervention group will receive an online psychoeducation treatment, in addition to pharmacological treatment prescribed by the psychiatrist.

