If clarification is required in relation to learning sessions or psychotherapy exercises, the participants will be able to interact with the psychiatric personnel through asynchronous messages. The user will get feedback on the status of the submission process (successful or not) and the messages will be stored in the BPTM environment.

The system will also be able to, automatically, identify potential alerts. Some examples of alert triggers are: a patient not having started the psychoeducation process after a certain period of time, and a patient “failing” the assessment questionnaire more than once. Patients should receive notifications based on their preferences (e.g., call center call, SMS, instant messaging, or email – to be decided). Alerts handled by the call center will be managed through the OSAREAN platform.

The content of the nine online psychoeducation sessions is as follows:Session 1. *What is bipolar disorder*?Information is provided to the patient about the nature of bipolar disorder (a description of the symptoms that characterize the disorder and biological mechanisms involved).Session 2. *Symptoms of the disorder*
The patient is taught to identify the characteristic symptoms of each phase of bipolar disorder.Session 3. *Course and prognosis of the disorder*
Risk factors that may contribute to worsening the course of the disorder are explained, as are factors related to a good prognosis.Session 4. *Pharmacological treatment for the disorder*
The mechanisms of action of medications are explained, as are potential side effects of the medication, in order to improve adherence and prevent the patient stopping the medication.Session 5. *Relapse prevention*: *risk and protective factors*
The patient is taught to recognize the symptoms that precede a relapse and risk factors that increase the likelihood of relapse, in order to improve the course of their illness.Session 6. *What can be done about a relapse*?It is explained to the patient that rapid identification of the prodromal symptoms and timely intervention can help to prevent relapse and bring him/her back to normal.Session 7. *Healthy lifestyle*
Tips to maintain a healthy lifestyle are provided, seeking to improve the health, quality of life, satisfaction and happiness of the patient.Session 8. *Toxic habits*

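### A single fixed block size of 4, where staff running the online arm know past assignments, could let up to 32% of assignments be known before enrolment; randomly varied, undisclosed block sizes would largely remove this

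*Protocol article*

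**What the plan says.** The Randomization section of the protocol article specifies "permuted block randomization with a block size of 4 and a 1:1 allocation using a computer-generated random sequence". It gives one size, mentions no variation and names no strata. On who makes the list it says: "The allocation sequence will be prepared by an independent person not otherwise involved in the trial".

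The Design section calls the study a "simple-blind randomized trial within a European project" without naming the blinded party. The same section states: "Both psychiatric personnel and patients should be able to view follow-up data (progress through the educational material". The Intervention program section adds, for queries about the sessions or exercises, that "the participants will be able to interact with the psychiatric personnel through asynchronous messages". Learning sessions and exercises belong to the online arm only; controls receive standard treatment. Staff in these roles therefore know which patients are in the online arm.

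The Participants section sets the target: "25 patients will be included in the experimental group (tele-care support) and 25 patients in the control group", 50 in all. The article does not say who enrols patients, whether they see earlier assignments, or how each assignment is released. An article commonly leaves such detail to the full protocol, and its absence is not counted as a fault here.

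**The concern.** In a permuted block of constant size, the last assignment is fixed by those before it, and sometimes the last two are. Anyone who knows the size, knows where the block began and has seen the earlier assignments can deduce the next one without access to the list. Independent preparation of the list protects against tampering and leaks, but not against this deduction.

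In a drug trial with a matching placebo, past assignments are hidden and the deduction fails. Here the arms differ openly and part of the staff know past assignments. If a person who decides whether and when to enrol a patient is among them, that person could hold back or bring forward patients according to the expected arm. Such selection makes the arms differ in prognosis before treatment begins. With 25 patients per arm, a few steered enrolments could move a mean. The planned ANCOVA on baseline and post-treatment scores would remove only the part of the difference that the baseline score captures.

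**Working it through.** **Inputs.** From the article: block size 4, ratio 1:1, 50 patients (25 + 25), two-sided 5% t test. Assumed, for the harm illustration only: the recruiter shifts the prognosis of a steered patient by 0.25 SD, in the direction of the expected arm. The article gives no predictability figure to reproduce.

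**1. Certain assignments with fixed blocks of 4.** A block with two A and two B has 6 equally likely orders.
- AABB and BBAA force the last two assignments: 2 orders × 2 = 4.
- The other four orders force only the last one: 4 orders × 1 = 4.
- Forced assignments per block: (4 + 4)/6 = 1.333 of 4, or 33.3%.
- Over 50 patients there are 12 full blocks and a half block of 2, in which nothing is forced: 12 × 1.333 = 16, and 16/50 = 32.0%.

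**2. Best-guess success with fixed blocks of 4.** The chance of guessing correctly at places 1 to 4 is 1/2, 2/3, 2/3 and 1.
- Per full block: (1/2 + 2/3 + 2/3 + 1)/4 = 0.708.
- Over 50 patients: (12 × 2.833 + 1/2 + 2/3)/50 = 35.17/50 = 0.703.

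**3. Varied block sizes.** These come from simulation of 50 patients (4,000 runs). The guesser knows the set of possible sizes, sees every past assignment and updates the unknown current size by Bayes' rule.

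| Scheme | Known with certainty | Best guess correct |
|---|---|---|
| Fixed 4 | 32.0% | 70.3% |
| Random 4 or 6 | about 5.7% | about 69.0% |
| Random 4, 6 or 8 | about 2.2% | about 67.7% |
| Simple randomization | 0% | 50% |

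**4. What this could do to the comparison when there is no treatment effect.** Let g be the best-guess success rate and c the share of assignments known with certainty. The rejection rate comes from the noncentral t distribution with 48 degrees of freedom and noncentrality bias × √(25/2).

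*Steering on every guess:* bias = 2 × 0.25 × (2g − 1).
- Fixed 4: 0.5 × (2 × 0.703 − 1) = 0.20 SD; two-sided rejection about 11%.
- Sizes 4, 6 and 8: 0.5 × (2 × 0.677 − 1) = 0.18 SD; about 9.4%.

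*Steering on certain assignments only:* bias = 2 × 0.25 × c.
- Fixed 4: 0.5 × 0.32 = 0.16 SD; about 8.6%.
- Sizes 4, 6 and 8: 0.5 × 0.022 = 0.01 SD; about 5.0%.

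These rates are for the unadjusted t test. ANCOVA would lower them to the extent that the baseline score reflects the steered prognosis.

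**5. Cost of an end imbalance.** Take the standardized difference at which 25:25 gives 80% power, 0.81 by the exact t calculation (the article states none). At that difference a 23:27 split gives about 79.7%, a loss of about 0.3 percentage points.

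**The case against.** Fixed blocks of 4 are common and give a valid randomization. The deduction needs three facts in one person's hands: the block size, every earlier assignment in the block, and the block's starting point. The article shows that staff running the online arm know assignments; it does not show that those who enrol do. Patients come from a regional mental health network, so several clinicians may refer into one list, and enrolment may be kept apart from treatment. Room for steering is also limited: entry has rating-scale cut-offs, and two clinicians make the diagnosis independently by structured interview. Finally, if a recruiter acts on every hunch, varying the block size changes little.

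Most of this stands. It makes 32% an upper bound, and it means the fix should not be sold as removing predictability. It does not defend the constant size. The stated scheme gives away certainty that a varied one would not, and the change costs almost nothing.

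Two stronger readings are tempting. A reader might infer that a third of assignments actually are known in advance; the article does not say who enrols or what they know. A reader might also infer that fixed blocks let a blinded rater work out a patient's arm. That does not follow: a rater who knows the other patients' arms is already unblinded, and the block size is not the cause.

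**Conclusion.** The point holds as a conditional risk with an inexpensive remedy. The article fixes "a block size of 4 and a 1:1 allocation" in a trial where staff running one arm know past assignments. If enrolling staff share that knowledge and know the block size, up to 32% of the 50 assignments (33% per full block) are certain before enrolment. Separate enrolling and treating staff, or one list shared by several clinics, would lower that share.

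The benefit of varying the sizes depends on how a recruiter would behave. Under the assumed 0.25 SD shift, bias falls from about 0.16 to 0.01 SD if only certain assignments are exploited, but only from about 0.20 to 0.18 SD if every guess is. The shift is an assumption, not a figure from the article, and the bias scales in proportion to it. Nothing in the article shows that selection has occurred or that the randomization is invalid.

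**What to change.** In the Randomization section, replace the fixed block size of 4 with permuted blocks of randomly varying size (for example 4, 6 and 8) and keep the 1:1 ratio. State that the sizes are not disclosed to recruiting, treating or assessing staff, and keep the actual sizes out of any document these staff receive until enrolment closes. If recruitment has begun, generate a new list for the remaining patients only.

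The cost is one new computer-generated list and one or two sentences. The final split may be slightly less even, for example 23:27, with negligible loss of power. Sizes 4 and 6 alone limit the end imbalance more but leave about 6% of assignments certain, against about 2%.
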